## Serious Adverse Experiences (SAE)

An SAE is defined as any AE occurring at any dose that results in any of the following outcomes:

- death
- a life-threatening adverse experience
- inpatient hospitalization or prolongation of existing hospitalization
- a persistent or significant disability/incapacity
- a congenital anomaly/birth defect

Other important medical events may also be considered an SAE when, based on appropriate medical judgment, they jeopardize the subject or require intervention to prevent one of the outcomes listed.

### Serious Adverse Experience Reporting

Study sites will document all SAEs that occur (whether or not related to study drug) per [UCSF CHR Guidelines](http://www.research.ucsf.edu/chr/Guide/Adverse_Events_Guidelines.asp" \l "2). The collection period for all SAEs will begin after informed consent is obtained and end after procedures for the final study visit have been completed.

In accordance with the standard operating procedures and policies of the local Institutional Review Board (IRB)/Independent Ethics Committee (IEC), the site investigator will report SAEs to the IRB/IEC.

# DISCONTINUATION And Replacement of subjects

## Early Discontinuation of Study Drug

A subject may be discontinued from study treatment at any time if the subject, the investigator, or the Sponsor feels that it is not in the subject’s best interest to continue. The following is a list of possible reasons for study treatment discontinuation:

Subject withdrawal of consent (or assent)

Subject is not compliant with study procedures

Adverse event that in the opinion of the investigator would be in the best interest of the subject to discontinue study treatment

Protocol violation requiring discontinuation of study treatment

Lost to follow-up

Sponsor request for early termination of study

Positive pregnancy test (females)

If a subject is withdrawn from treatment due to an adverse event, the subject will be followed and treated by the Investigator until the abnormal parameter or symptom has resolved or stabilized.

All subjects who discontinue study treatment should come in for an early discontinuation visit as soon as possible and then should be encouraged to complete all remaining scheduled visits and procedures.

All subjects are free to withdraw from participation at any time, for any reason, specified or unspecified, and without prejudice.

Reasonable attempts will be made by the investigator to provide a reason for subject withdrawals. The reason for the subject’s withdrawal from the study will be specified in the subject’s source documents Refer to Section 10 for early termination procedures.

## Withdrawal of Subjects from the Study

A subject may be withdrawn from the study at any time if the subject, the investigator, or the Sponsor feels that it is not in the subject’s best interest to continue.

All subjects are free to withdraw from participation at any time, for any reason, specified or unspecified, and without prejudice.

Reasonable attempts will be made by the investigator to provide a reason for subject withdrawals.  The reason for the subject’s withdrawal from the study will be specified in the subject’s source documents.  As noted above, subjects who discontinue study treatment early (i.e., they withdraw prior to Visit 2) should have an early discontinuation visit. Refer to Section 10 for early termination procedures.  Subjects who withdraw after Visit 2 but prior to Visit 3 should be encouraged to come in for a final visit (and the procedures to be followed would include those for their next scheduled visit).

## Replacement of Subjects

Subjects who withdraw from the study treatment will not be replaced.

Subjects who withdraw from the study will not be replaced.

# PRotocol Violations

A protocol violation occurs when the subject, investigator, or Sponsor fails to adhere to significant protocol requirements affecting the inclusion, exclusion, subject safety and primary endpoint criteria. Protocol violations for this study include, but are not limited to, the following:

Failure to meet inclusion/exclusion criteria

Use of a prohibited concomitant medication

Failure to comply with Good Clinical Practice (GCP) guidelines will also result in a protocol violation. The Sponsor will determine if a protocol violation will result in withdrawal of a subject.

When a protocol violation occurs, it will be discussed with the investigator and a Protocol Violation Form detailing the violation will be generated. This form will be signed by a Sponsor representative and the Investigator. A copy of the form will be filed in the site’s regulatory binder and in the Sponsor’s files.

# STATISTICAL METHODS AND CONSIDERATIONS

Prior to the analysis of the final study data, a detailed Statistical Analysis Plan (SAP) will be written describing all analyses that will be performed. The SAP will contain any modifications to the analysis plan described below.

## Data Sets Analyzed

All eligible patients who are randomized into the study and receive an interscalene block will be included in the safety analysis.

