# STUDY DESIGN

## Study Overview

This is a single center, blinded, randomized trial. 208 of subjects are planned. Each subject will be administered a single injection of ropivacaine 0.5% either intraplexus or extraplexus prior to their shoulder surgery. Subjects will be assigned to the treatment group in random order. Evaluations will be taken in one-minute intervals after placement of the block until loss of motor or sensation is observed. Subjects will undergo a standardized general anesthetic. Sensory exam will be reevaluated in the recovery room. Patients will be contacted via telephone on post-operative day 1. Data from their 1 week postoperative visit will be recorded.

Screening data will be reviewed to determine subject eligibility. Subjects who meet all inclusion criteria and none of the exclusion criteria will be entered into the study.

The following treatment regimens will be used:

Experimental treatment –interscalene injection performed intraplexus (between C5-C6 nerve roots)

Comparator – interscalene injection performed extraplexus (anterior and posterior to brachial plexus in interscalene groove)

Total duration of subject participation will be two weeks. Total duration of the study is expected to be 24 months.

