## Exclusion Criteria

1. Pregnant during participation in the study.
2. Non-English speaking
3. Any contraindication for regional anesthesia, such as an allergy to local anesthetics or opioids, coagulopathy or severe thrombocytopenia, infection at puncture sites, pre-existing neuropathy in operative limb, need for postoperative nerve function monitoring
4. History of pulmonary disease or low baseline oxygen saturation
5. History of dementia
6. High preoperative opioid requirements

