# STUDY TREATMENTS

## Method of Assigning Subjects to Treatment Groups

Up to 208 eligible patients will be randomly assigned to intraplexus or extraplexus treatment groups in a 1:1 ratio using an Excel computer-generated randomization scheme developed by the study data management provider. The allocated group will be written on a paper in a sealed, opaque envelope that will be provided only to the anesthesia provider performing the block.

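### As worded, the safety analysis covers only eligible patients, so a randomized patient who received the block and is later found ineligible drops out of the safety summaries

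*Protocol*

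**What the plan says.** Data Sets Analyzed (section 14.1) consists of one sentence: "All eligible patients who are randomized into the study and receive an interscalene block will be included in the safety analysis". A patient must therefore meet three conditions to be in the safety analysis: be eligible, be randomized and have received a block. The protocol defines no other analysis set.

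The Protocol Violations section gives "Failure to meet inclusion/exclusion criteria" as one of its two named examples of a violation. On the consequence it says: "The Sponsor will determine if a protocol violation will result in withdrawal of a subject". It does not say whether the data of such a patient stay in any analysis.

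The Exclusion Criteria include "History of pulmonary disease or low baseline oxygen saturation", "coagulopathy or severe thrombocytopenia, infection at puncture sites, pre-existing neuropathy in operative limb" and "Pregnant during participation in the study".

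Two passages describe who enters the trial. Study Overview says: "Subjects who meet all inclusion criteria and none of the exclusion criteria will be entered into the study". Method of Assigning Subjects to Treatment Groups says: "Up to 208 eligible patients will be randomly assigned to intraplexus or extraplexus treatment groups in a 1:1 ratio".

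**The concern.** Safety is normally assessed in everyone who was exposed. In this trial exposure is complete once the block has been given, and finding afterwards that a criterion was not met does not undo it. A rule that depends on eligibility removes exposed patients on grounds that can be established after treatment.

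The removal need not be neutral. Several exclusion criteria exist because they bear on the risks of the block, so a patient who breaches one of them can be more likely than others to have the harms the trial tabulates. The Risk / Benefit Assessment calls the serious harms of nerve blockade very rare. With harms that rare, a single omitted event can be the difference between an arm that shows the event and an arm that shows none.

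**Working it through.** **1. Does the rule, read literally, leave anyone out?** Take a patient who was randomized, received the block and was later found to have breached a criterion.

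- Randomized: met.
- Received a block: met.
- Eligible: not met.

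The patient is outside the set.

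**2. Does the protocol provide for such a patient?** Yes. Protocol Violations names this case. One criterion, "Pregnant during participation in the study", covers the whole period of participation and so can be breached after the block.

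**3. Does anything put the patient back?**

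| Place in the protocol | What it covers | Widens the safety set? |
| --- | --- | --- |
| Clinical Assessments, Adverse Events | Recording of adverse events during the study | No: collection only |
| Serious Adverse Experience Reporting | Documentation of all serious events and reporting to the ethics board | No: reporting only |
| Analysis of Secondary Endpoints | Safety tables by treatment group | No: names no population |
| Protocol Violations | Sponsor decides on withdrawal | No: silent on analysis |

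**4. Do the exclusions bear on the harms studied?** The first three rows match outcomes listed under Safety Evaluations. The fourth matches a background risk in the Risk / Benefit Assessment that is not in that list.

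| Exclusion criterion | Related harm |
| --- | --- |
| Pulmonary disease or low saturation | Shortness of breath |
| Pre-existing neuropathy in the limb | Nerve injury, paresthesias |
| Infection at puncture sites | Infection at insertion site |
| Coagulopathy or severe thrombocytopenia | Bleeding at the puncture site |

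Other exclusions, such as not speaking English, carry no evident added risk from the block.

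**5. How much could one patient matter?** The protocol has no figure of its own on this point to reproduce. The input is the planned size: 208 patients at 1:1, so 208/2 = 104 per arm, which agrees with the synopsis.

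The exact one-sided 95% upper bound U for x events in n patients solves P(X ≤ x | n, U) = 0.05.

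- With the patient kept, 1/104: (1 − U)^104 + 104·U·(1 − U)^103 = 0.05 gives U ≈ 0.0448, about 4.5%. Check: 0.0085 + 0.0415 = 0.0500.
- With the patient dropped, the denominator also falls by one, 0/103: U = 1 − 0.05^(1/103) = 0.0287, about 2.9%.

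If instead 2 of 104 had an event and one of them was ineligible, the observed rate would go from 2/104 = 1.9% to 1/103 = 1.0%.

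**6. How many patients might be affected?** The protocol gives no rate. Assuming that 1% to 5% of treated patients prove ineligible, the number left out is 208 × 0.01 = 2.08 to 208 × 0.05 = 10.4, or about 2 to 10. That range is an assumption, not a forecast.

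**The case against.** The strongest reply is that *eligible* is only descriptive. Study Overview admits only subjects who satisfy the criteria, and the randomization section uses the same adjective for everyone assigned: "Up to 208 eligible patients will be randomly assigned to intraplexus or extraplexus treatment groups in a 1:1 ratio". On that usage, eligible patients who are randomized simply means the enrolled patients. The sentence is also phrased as an inclusion and describes no later eligibility review or removal. This reading is possible and lowers confidence in what the authors intended. It does not cure the wording, because the protocol separately provides for enrolled subjects who failed the criteria, and for them the word decides the matter.

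The second reply is that the damage is limited. History, examination, oximetry and the pregnancy test all come before randomization at Visit 1, so many breaches would be caught before the block. Adverse events are captured throughout, serious ones go to the ethics board, and each violation generates a form. All of this stands. A reader might infer that ineligible patients' harms go unreported, but the protocol does not support that: what is lost is their place in the analysed summaries.

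The third reply is that a later SAP may change the plan, as the protocol allows. That is true, but the protocol has stated a restrictive rule, and it holds unless someone alters it.

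Two further inferences are tempting and go beyond the document. One is that patients found ineligible are often at higher risk; no frequency is given and some criteria are unrelated to block risk, so only *can be* is justified. The other is that ineligibility is most likely to surface when a complication prompts a record review. That could happen, but nothing in the protocol says how breaches come to light, so exclusion driven by the event itself cannot be asserted.

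**Conclusion.** Wrong as written, with moderate confidence. The literal rule removes exposed patients from the safety analysis, the protocol provides for such patients, and no other section restores them. Confidence is not higher because the authors may have meant the word descriptively.

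The size is unknown. The change from 1/104 to 0/103 (upper bound about 4.5% to about 2.9%) is a constructed case. It assumes full enrolment of 104 per arm and one ineligible treated patient who also has the event, and the protocol gives no probability for that combination. It does not show that the trial's safety results will be understated: dropping an ineligible patient without an event raises the observed rate slightly, for example from 1/104 to 1/103. The sample size and the log-rank comparison of onset times are unaffected.

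**What to change.** In Data Sets Analyzed, delete the word *eligible*, keep the conditions of randomization and receipt of an interscalene block, and add at the end of the sentence: whether or not they are later found to meet the entry criteria.

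The change needs one word struck and one clause added through the ordinary amendment route. It requires no new data, since adverse events are already collected for everyone in the study, and it leaves the planned summary by treatment group as it is. If the word was only ever descriptive, the edit changes nothing in practice and removes the ambiguity. Any SAP should carry the same definition.

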### Adverse Events

Information regarding occurrence of adverse events will be captured throughout the study. Duration (start and stop dates), severity/grade, outcome, treatment and relation to study drug will be recorded on the case report form (CRF).

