## Analysis of Secondary Endpoints

Categorical data will be analyzed using Chi squared analysis or Fischer's exact test, depending on sample size. Comparison of means will be performed using the independent sample t-test or the Mann-Whitney U test, depending on distribution. A p-value of 0.05 or smaller will be considered statistically significant.

Safety and tolerability data will be summarized by treatment group. Adverse event rates will be coded by body system and MedDra classification term.  Adverse events will be tabulated by treatment group and will include the number of patients for whom the event occurred, the rate of occurrence, and the severity and relationship to study drug.

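### The safety analysis set is conditioned on eligibility, so it can be read as leaving out a randomized patient who was blocked and later found ineligible

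*Protocol*

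**What the plan says.** The protocol defines a single analysis set, under Data Sets Analyzed: "All eligible patients who are randomized into the study and receive an interscalene block will be included in the safety analysis". That sets three conditions: eligible, randomized and blocked.

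Eligibility is tied to entry elsewhere. Study Overview states: "Subjects who meet all inclusion criteria and none of the exclusion criteria will be entered into the study". Method of Assigning Subjects to Treatment Groups uses the word in the same way: "Up to 208 eligible patients will be randomly assigned to intraplexus or extraplexus treatment groups in a 1:1 ratio".

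The Protocol Violations section lists "Failure to meet inclusion/exclusion criteria" among its foreseen violations and leaves it to the sponsor whether a violation leads to withdrawal.

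Collection of safety data has no eligibility limit. The Adverse Events paragraph under Clinical Assessments says: "Information regarding occurrence of adverse events will be captured throughout the study". For serious events, Serious Adverse Experience Reporting says: "The collection period for all SAEs will begin after informed consent is obtained". The adverse event tables described under Analysis of Secondary Endpoints "will include the number of patients for whom the event occurred, the rate of occurrence", by treatment group.

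**The concern.** A safety population is normally fixed by exposure: whoever received the intervention is counted. Here exposure is necessary but, on the plain wording, not sufficient, because the patient must also be eligible. A patient randomized and blocked in error has been exposed to the technique under study and has had adverse events collected, but could be dropped when the tables are made. Because the tables give both a count and a rate, that patient would leave the numerator and the denominator together.

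Patients who fail the entry criteria are not a neutral group for safety. Several exclusions exist because the block is riskier, or its complications harder to interpret, in those patients. If they are the ones left out, the harms they are most prone to are the ones that could be understated.

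**Working it through.** The protocol attaches no figure to this point, so there is none to reproduce. The check is mainly a comparison of sections, followed by one illustration.

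**Step 1: can an ineligible patient be blocked and remain in the study?** Yes. Protocol Violations names failure of the entry criteria as a violation and does not make withdrawal automatic. Visit 1 places history, examination, oximetry, randomization and block on the day of surgery, so an error found later would be found after exposure.

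**Step 2: does that patient meet the definition of the safety set?** The patient is randomized and has received a block, so two of the three conditions hold. Whether the third holds depends on what eligible means:

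- If it means satisfying the entry criteria, as the entry rule in Study Overview suggests, the condition fails and the patient is outside the set.
- If it means accepted into the trial, the condition holds for everyone randomized. The word then adds nothing.

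**Step 3: are the excluded patients neutral for safety?** Comparing Exclusion Criteria with Safety Evaluations gives three matches:

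| Exclusion criterion | Harm on the safety list |
| --- | --- |
| "History of pulmonary disease or low baseline oxygen saturation" | Shortness of breath |
| Infection where the needle enters | Infection at the insertion site |
| Existing neuropathy of the operative limb | Nerve injury (lasting deficit) |

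**Step 4: how much could one patient matter?** The documents give no rate of enrolment in error, so no bias can be calculated. The following shows leverage only. Inputs:

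- 208 patients at 1:1, so 208/2 = 104 per arm (the synopsis also gives 104).
- Risk / Benefit Assessment calls the serious complications of nerve blockade very rare, so an arm with a single such event is plausible.
- Assumption: that one event falls in the arm's one ineligible patient.

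Patient counted:

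- Rate = 1/104 = 0.96%.
- The one-sided exact (Clopper-Pearson) 95% upper limit solves (1 − p)^104 + 104p(1 − p)^103 = 0.05, giving p = 4.48%.

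Patient left out:

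- Rate = 0/103 = 0%.
- Upper limit = 1 − 0.05^(1/103) = 2.87%.

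The arm goes from one event to none, and the upper limit falls by 4.48 − 2.87 = 1.61 percentage points. The protocol plans counts and rates, not confidence limits; the limits are shown only to put the change on a scale.

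**The case against.** The strongest reply is that the sentence says who will be included and never says that anyone is excluded. It contains no word such as only and no rule for removing patients after randomization. Since the protocol elsewhere calls the patients to be randomized eligible, the sentence may simply mean enrolled patients who were blocked. The collection and tabulation sections point the same way, because none limits adverse events to eligible patients. Protocol Violations deals with entry failures through a violation form and a sponsor decision, and does not mention analysis. This stands to the extent that one cannot say the protocol does leave such patients out; it can be read that way. It does not rescue the word: on the benign reading it is superfluous, and on the other it is wrong.

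A second reply is that the SAP, which the protocol promises and allows to modify the plan, is where violators are assigned to analysis sets. It is true that the absence of other analysis sets from the protocol is no defect. This sentence, however, is a stated condition, and on its stricter reading the SAP would have to reverse it.

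A third reply is that few patients could be affected. History, examination and oximetry precede randomization at Visit 1, an infected site would be visible to the person performing the block, both arms receive the same drug and dose, and nothing suggests that errors would differ between arms. That stands, and it limits the size of the point.

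**Conclusion.** The point holds as a minor defect of wording with a possible safety consequence. The protocol's only defined analysis set makes eligibility a condition of the safety analysis, although the protocol itself foresees patients who fail the entry criteria and may already have been blocked.

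A reader might infer that the plan excludes these patients and that reported harms will therefore be too low. The documents do not support that. There is no explicit exclusion, the word has a benign reading, and no rate of erroneous enrolment is given. Nor would harms go unrecorded: adverse events are captured and serious ones reported to the ethics board for all participants. What is at risk is their place in the comparative tables.

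The effect is confined to patients enrolled in error, whose number is unknown and probably small. The change from 1/104 to 0/103 is a constructed worst case, resting on the assumption that an arm's single event occurs in its single ineligible patient; it is not an estimate. The primary endpoint and the sample size do not depend on this sentence.

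**What to change.** In Data Sets Analyzed, delete the word eligible, so that the safety analysis covers every randomized patient who receives an interscalene block, and carry the same definition into the SAP. Patients found ineligible after the block stay in the adverse event tables and are still documented as protocol violations.

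The cost is one word. Procedures, data collection, sample size and the primary analysis are unchanged.
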